#### 5.5.2. Secondary Outcomes

Secondary outcomes include a broad range of bleeding-related outcomes, thrombotic complications, and postoperative complications, and healthcare resource utilization. Bleeding-related outcomes include preoperative blood transfusion, the number of PRBCs administered (1, 2, 3, or ≥4 units), lowest postoperative Hb and Ht levels within 24 h postoperatively, Hb decrease (ΔHb) (defined as the difference between preoperative Hb (measured at the ED) and the lowest postoperative Hb within 24 h), the bleeding index (defined as ΔHb plus the number of PRBC transfused between the ΔHb period), the number of patients experiencing a Hb decrease of more than 2 mmol/L. Estimated intraoperative blood loss will not be recorded, as it is considered too subjective, prone to outcome reporting bias, and highly susceptible to inter-rater variability. Clinical complications such as reoperation due to postoperative bleeding or infection, sciatic neuropraxia due to postoperative bleeding or infection, postoperative hematoma, and postoperative anemia will also be recorded. Lastly, administration of tranexamic acid, fibrinogen, or platelet concentrates will also be assessed.

Thrombotic complications recorded in this study comprise myocardial infarction (confirmed by electrocardiogram), stroke (confirmed by CT), pulmonary embolism (confirmed by CT-Angiography), deep vein thrombosis (confirmed by ultrasound), and peripheral arterial thrombosis (confirmed by CT-Angiography).

Other postoperative complications as determined by the Dutch Hip Fracture Audit guidelines will be assessed and include pressure ulcers, delirium, deep or superficial surgical wound infections, wound fluid leakage, days of wound fluid leakage, congestive heart failure, and in-hospital falls (all diagnosed by the attending physician or geriatrician) [54]. Additional complications include pneumonia (confirmed by chest radiograph or positive sputum culture), urinary tract infections (confirmed by a positive urine culture), renal insufficiency (defined as a >24 mL/min/1.73 m^2^ decrease in eGFR compared to admission), in-hospital mortality (recorded in hospital records), and 30-day mortality (determined through municipality records) [54].

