Additional secondary outcomes include: hospital length of stay (in days, defined as the time between ED presentation and discharge from hospital or in-hospital death), time to surgery (in hours, from ED presentation to start of surgery), hours between last DOAC intake and start of surgery (in hours, defined as the interval between the last reported DOAC intake and the start of surgery), time until DOAC therapy is restarted after surgery (in hours, defined as the time between end of surgery and first postoperative DOAC dose), total time without DOAC therapy (in hours, defined as the time between last DOAC intake and the first postoperative DOAC dose), surgical duration (in minutes, recorded from incision to closure), and discharge destination (categorized as: home, home with assistance for ADL, temporary skilled nursing care, geriatric rehabilitation care, or a long term geriatric care facility).

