#### 5.8.2. Secondary Outcomes

Secondary outcomes will be analyzed according to the type and distribution of each variable. Continuous variables (i.e., Hb decrease, bleeding index, surgery duration, time to DOAC restart, hospital length of stay) will first be assessed for normality using graphical methods (e.g., histograms). Normally distributed outcomes will be analyzed using parametric tests, specifically independent-sample t-tests. If the distribution is non-normal, non-parametric methods, such as the Mann–Whitney U test, will be applied. Ordinal or categorical variables with more than two categories, such as the number of packed red cell units transfused, will be analyzed using the Chi-square test. Binary outcomes, including thromboembolic events, postoperative complications, and a Hb decrease of more than 2 mmol/L, will be analyzed using Chi-square tests, or Fisher’s exact test in cases where expected cell counts are less than five.

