### 5.9. Missing Data

Because of the prospective registration of predefined variables and regular quality checks, we expect minimal missing data. If missing data occur, we will assess their extent and mechanism (missing completely at random, missing at random, or missing not at random). When appropriate, we will apply multiple imputation using chained equations to minimize bias and preserve statistical power.

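### Time to DOAC restart is tested as an ordinary continuous variable, but patients who never restart have no value, so the planned test compares restarters only

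*Protocol article*

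**What the plan says.** Section 5.5.2 of the protocol article places two intervals among the additional secondary outcomes, both ending at the same event. One starts when the operation ends: "time until DOAC therapy is restarted after surgery (in hours, defined as the time between end of surgery and first postoperative DOAC dose". The other starts earlier, before the operation, and is worded as follows: "total time without DOAC therapy (in hours, defined as the time between last DOAC intake and the first postoperative DOAC dose".

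Neither has a rule for a patient with no postoperative dose. Length of stay, in the same list, does have a rule for death: it is "defined as the time between ED presentation and discharge from hospital or in-hospital death".

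Section 5.8.2 assigns the analysis by variable type. Its list reads "Continuous variables (i.e., Hb decrease, bleeding index, surgery duration, time to DOAC restart, hospital length of stay", so time to restart is named. Total time without DOAC is not named, but it is measured in hours and would fall under the same rule by type. For the normal case the article states: "Normally distributed outcomes will be analyzed using parametric tests, specifically independent-sample t-tests". For the other case it allows alternatives: "non-parametric methods, such as the Mann–Whitney U test, will be applied".

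Section 5.9 gives one general rule for missing data: "When appropriate, we will apply multiple imputation using chained equations to minimize bias and preserve statistical power".

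**The concern.** A t-test or Mann–Whitney test needs one number per patient. Patients who die first, or whose DOAC is stopped for good or replaced, have no restart time to enter. Unless a value or rank is assigned to them, they leave the comparison.

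That loss is unlikely to be random. Death and serious bleeding are plausible reasons for not restarting, and bleeding is the harm under study. The comparison then depends on an event after surgery that the timing policy may itself influence. A cohort in which more of the slow or complicated patients never restart loses more of its longest times and can look better than it is. Readers will look at time off anticoagulant when they interpret any thrombotic or bleeding difference, so a restart comparison among restarters only could mislead them.

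**Working it through.** **1. Are patients without a value foreseeable?** Yes. Section 5.5.2 records "in-hospital mortality (recorded in hospital records), and 30-day mortality (determined through municipality records", together with postoperative hematoma and reoperation for bleeding. Section 5.6 takes the data from hospital records and describes no follow-up of medication after discharge. Loss at discharge is therefore an inference; loss through death or permanent stop is not.

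**2. Does Section 5.9 fill the gap?** No. Multiple imputation estimates a value that exists but was not recorded. A restart that never took place is not such a value.

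**3. Size.** The documents give no restart times or non-restart rates, so there is no stated figure to reproduce. The illustrations below rest on assumptions.

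*Illustration A: non-restart linked to bleeding.* From Section 5.7, 15% and 10% are borrowed as bleeding rates for a higher- and a lower-bleeding cohort (they are transfusion rates, delayed and early). Assumed: mean restart 72 h with bleeding and 36 h without, and 5% of non-bleeders never restarting.

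If everyone restarted: 0.15×72 + 0.85×36 = 41.4 h against 0.10×72 + 0.90×36 = 39.6 h, a true gap of 1.8 h.

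Among restarters, with bleeding rate b and share r of bleeders not restarting:

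mean = [b(1−r)×72 + (1−b)×0.95×36] / [b(1−r) + (1−b)×0.95]

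For example, with b = 0.15 and r = 0.20: (0.12×72 + 0.8075×36)/0.9275 = 40.66 h.

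| Bleeders not restarting (higher / lower cohort) | Higher, h | Lower, h | Gap, h |
|---|---|---|---|
| 0% / 0% | 41.64 | 39.77 | 1.87 |
| 20% / 20% | 40.66 | 39.08 | 1.58 |
| 80% / 80% | 37.29 | 36.82 | 0.47 |
| 40% / 20% | 39.61 | 39.08 | 0.53 |
| 50% / 20% | 39.06 | 39.08 | −0.02 |
| 60% / 20% | 38.49 | 39.08 | −0.59 |
| 80% / 20% | 37.29 | 39.08 | −1.79 |

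With equal non-restart by bleeding status, the gap shrinks but keeps its sign. It reverses only when about half or more of the higher cohort's bleeders never restart, against 20% in the other.

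*Illustration B: unequal observation windows.* Same bleeding rates; log-normal restart with medians 72 h and 36 h and log-SD 0.5; 187 per group; 2,000 simulated studies. If restarts are seen only up to 72 h in the higher-bleeding cohort and 120 h in the other, 14.5% and 2.3% are unseen. True means of 46.9 and 44.8 h become observed means of 37.4 and 42.3 h. Mann–Whitney on restarters calls the higher-bleeding cohort significantly faster in 30% of studies, against 0.4% when non-restarters are kept as the longest ranks. With a 72 h window in both cohorts, the observed means are 37.4 and 36.9 h: diluted, not reversed.

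*Illustration C: no true difference.* Same log-normal restart in both cohorts (median 48 h, log-SD 0.6): mean 48×exp(0.6²/2) = 57.5 h. If only the fastest share q is observed, the mean is 57.5×Φ(z_q − 0.6)/q. This gives 48.0 h at q = 0.90 and 51.5 h at q = 0.95, a spurious 3.5 h. The corresponding medians are 44.5 and 46.2 h, a gap of 1.7 h.

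**4. Total time without DOAC.** It is the sum of intake-to-surgery hours, the operation and surgery-to-restart hours. Section 5.8.1 makes the first part less than 24 h in one per-protocol cohort and 24 h or more in the other. Part of any difference therefore follows from how the cohorts are defined.

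**5. Primary outcome.** The sample size reproduces: (0.15×0.85 + 0.10×0.90)×(1.645 + 1.282)²/(0.05 + 0.05)² = 186.3, hence 187 per group and 374 in total. No restart time enters it.

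**The case against.** The strongest reply is that nothing in the article says non-restarters are dropped or imputed. Section 5.8.2 allows non-parametric methods in general, so a rank analysis placing non-restarters last would fit. Section 5.9 imputes only where appropriate. A journal article may leave the coding of such patients to a fuller document. This stands in part: dropping is a consequence of the named tests, not a stated rule. But the article fixes both the endpoint and the test. The t-test branch has no place for a patient without a time, and the histogram that chooses the branch would itself show restarters only.

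A reader might infer that the cohort with more bleeding will look quicker to restart. The documents do not support that. Reversal needs non-restart or observation windows to differ between cohorts, and nothing in the article establishes either. Section 3 hopes for a shorter stay after early surgery, but stay is counted from ED presentation and includes the preoperative wait, so it says little about the window after surgery. Illustration C gives one cohort twice as many non-restarters by assumption; if that is taken to be early surgery, the only related rates in the article (transfusion 10% early, 15% delayed) point the other way.

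A reader might also call it an error that total time without DOAC includes the preoperative hours. It is not. Total interruption is a real consequence of each policy, and Section 5.5.2 already lists intake-to-surgery and surgery-to-restart times separately.

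Finally, the stakes are modest: neither interval appears among the secondary objectives in Section 4.2, and no decision is tied to them.

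**Conclusion.** The point holds for time to DOAC restart. It is undefined for patients who die or permanently stop the drug before a first postoperative dose, and possibly for those discharged before restarting. The named tests, applied as written, compare restarters only. The expected effect is dilution of a difference. A distorted direction is possible only if non-restart or the observation window differs between cohorts. The size cannot be derived from the documents. Under the assumed inputs above, the change in the gap between cohort means ranges from a fraction of an hour to about 7 h (from +2.1 to −4.9 h in the first scenario of illustration B, the most extreme shown).

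Total time without DOAC shares the gap for non-restarters, although its test is inferred from its type, not named. Its preoperative component is legitimate but limits what a between-cohort test can show. The consequence is confined to these additional secondary outcomes. A change is worth making because a better analysis costs almost nothing.

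**What to change.** In Section 5.8.2, take time to DOAC restart out of the continuous list and specify one of two analyses from end of surgery:

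- cumulative incidence of restart, with death and permanent stop as competing events, and censoring at discharge if later doses are not recorded; or
- the proportion restarted by fixed, prespecified times (for example 48 h and 72 h), with all patients in the denominator.

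If discharge censors, state that this assumes discharge is unrelated to the prospect of restarting. Report per cohort the number never restarted and, where known, the reason. State in Section 5.9 that doses that never occurred are not imputed.

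Handle non-restarters in total time without DOAC in the same way. Present it descriptively beside the two component intervals, noting that part of any per-protocol difference follows from the group definition.

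The cost is a few lines of wording. Restart, discharge and death are already recorded for other outcomes; permanent stop may need one extra field. The small downside is that a curve or proportions replace a single mean or median.

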### 4.2. Secondary Objectives

-To investigate the effect on other bleeding-related outcomes in this population (i.e., preoperative blood transfusions, pre- and postoperative hemoglobin difference, the bleeding index, amount of packed red blood cells administered, reoperation due to postoperative bleeding or infection, sciatic neuropraxia due to postoperative bleeding or infection, postoperative anemia and postoperative hematoma).-To investigate the effect on thromboembolic outcomes in this population (such as acute myocardial infarction, stroke, pulmonary embolism, peripheral arterial thrombosis, and deep venous thrombosis).-To investigate the effect on postoperative complications in this population (i.e., wound fluid leakage, pressure ulcer, congestive heart failure, delirium, renal insufficiency, pneumonia, urinary tract infections, deep or superficial surgical wound infection, and in-hospital falls).-To investigate the effect on in-hospital and 30-day mortality in this population.-To investigate the effect on hospital length of stay and discharge destination in this population.

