### 5.3. Eligibility Criteria

Patients are eligible for inclusion if they present with an isolated hip fracture classified as AO/OTA 31A or 31B, requiring surgical intervention, are actively using DOACs and have taken their DOAC within 24 h before ED presentation (Figure 1) [46]. Exclusion criteria include pathological or periprosthetic fractures, fractures sustained more than 24 h before ED presentation, and transfers to another hospital. Patients with hematologic disorders or disruptions (i.e., thalassemia, sickle cell disease, aplastic anemia, myelodysplastic syndromes, or leukemia) will also be excluded, as will those using a non-approved DOAC (i.e., betrixaban) by the European Medicines Agency. Patients presenting to the ED more than 24 h after fracture occurrence are excluded, as delayed presentation introduces uncertainty regarding active DOAC exposure in the early surgery cohort. In such cases, anticoagulant activity may have substantially declined irrespective of institutional surgical timing protocols. Although this exclusion may limit generalizability and introduce selection bias, it was considered necessary to preserve internal validity and ensure meaningful comparability between early and delayed surgery cohorts.

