### 5.4. Baseline Characteristics

The following baseline characteristics will be collected: age, sex, preoperative estimated glomerular filtration rate (eGFR in mL/min/1.73 m^2^), preoperative hemoglobin (Hb in mmol/L), preoperative hematocrit (Ht in L/L), type of DOAC (apixaban, edoxaban, rivaroxaban, or dabigatran), DOAC dosage, DOAC indication, hours since last DOAC intake, concurrent use of antiplatelet medication (yes/no), and the specific type of concurrent antiplatelet or anticoagulant medication used. Frailty indicators include a prior diagnosis of dementia (by a geriatrician or general practitioner), Body Mass Index (BMI in kg/m^2^), Short Nutritional Assessment Questionnaire (SNAQ) score, Clinical Frailty Scale (CFS), Charlson Comorbidity Index (CCI), American Society of Anesthesiologists (ASA) score, number of daily medications, pre-fracture living situation (independently at home, with assistance in Activities of Daily Living (ADL), or in institutional care facility), household composition (living alone, with a partner, or with family), pre-fracture mobility (based on the Fracture Mobility Score), and Katz-6 ADL score [47,48,49,50,51,52]. Fracture characteristics include the type of fracture (based on AO/OTA classification) and the surgical procedure performed (hemiarthroplasty, total hip arthroplasty, intramedullary nail, sliding hip screw, or cannulated hip screw) [46]. Lastly, the type of anesthesia (general or spinal), any preoperative use of tranexamic acid, fibrinogen, or platelet concentrates, and DOAC reversal agents (idarucizumab or andexanet alfa) will be registered. In addition, patients whose surgery was delayed for reasons unrelated to DOAC use will be documented, along with the specific reason for the delay. Measurement of DOAC plasma levels is not part of routine care in the participating centers and is therefore not included.

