### 5.8. Statistical Analysis

#### 5.8.1. Primary Outcome

The primary outcome is postoperative blood transfusion in hip fracture patients on DOACs. To assess non-inferiority of early surgery within 24 h compared to delayed surgery 24 h or more after last DOAC intake, the risk difference in transfusion requirement between both groups will be calculated with a corresponding one-sided 95% CI. Non-inferiority will be concluded if the upper bound of the one-sided 95% CI does not exceed the predefined non-inferiority margin of 5%.

In addition, a multivariable logistic regression analysis will be performed to estimate the adjusted odds ratio (aOR) and associated 95% CI for transfusion requirement, adjusting for potential confounders. Based on literature and expert-opinion, the following variables will be considered for inclusion in the regression model: sex, preoperative Hb, Clinical Frailty Scale, and type of surgical procedure [59,60,61,62]. Given a total sample size of 374 and an expected event rate of 15%, approximately 56 events are anticipated, allowing for inclusion of up to five independent variables, in accordance with standard rules to prevent model overfitting.

The primary analysis will follow a per-protocol approach, in which patients will be analyzed based on adherence to the surgical timing protocol of their respective hospital (i.e., within 24 h for School “A” centers and after 24 h or more for School “B” centers). Patients whose surgical timing deviates from this hospital protocol will be identified and excluded from the per-protocol analysis (Figure 2). In addition, an intention-to-treat (ITT) analysis will be conducted, in which patients will be analyzed according to the timing policy of their admitting hospital, regardless of actual timing. This ITT analysis will serve to assess the robustness of the findings, while preserving the effect of quasi-randomization and limiting the risk of confounding by indication. As a sensitivity analysis, propensity score matching will be applied to further assess robustness of the primary findings. This analysis will allow comparison of results obtained using propensity score matching with those derived from the natural experiment design and provide additional insight into the methodological value of the natural experiment approach.

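### Discharge destination is compared without using the recorded pre-fracture living situation, so a return to an institution cannot be told apart from a new admission to one

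*Protocol article*

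**What the plan says.** Section 4.2 makes this a stated objective: "To investigate the effect on hospital length of stay and discharge destination in this population". Section 5.5.2 defines the outcome as "discharge destination (categorized as: home, home with assistance for ADL, temporary skilled nursing care, geriatric rehabilitation care, or a long term geriatric care facility"). These are absolute destinations, and none is defined relative to where the patient came from.

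Section 5.4 records the matching baseline variable: "pre-fracture living situation (independently at home, with assistance in Activities of Daily Living (ADL), or in institutional care facility"). Section 5.3 does not exclude institutional residents. The exclusions that it opens with are clinical and logistical ("Exclusion criteria include pathological or periprosthetic fractures, fractures sustained more than 24 h before ED presentation, and transfers to another hospital"), and those that follow concern blood disorders and non-approved DOACs.

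For the analysis, section 5.8.2 says: "Ordinal or categorical variables with more than two categories, such as the number of packed red cell units transfused, will be analyzed using the Chi-square". Discharge destination is not named there, but it has five categories and so falls under that rule. The adjustment and matching in section 5.8.1 belong to the transfusion outcome. There "the following variables will be considered for inclusion in the regression model: sex, preoperative Hb, Clinical Frailty Scale, and type of surgical procedure", a list without living situation, and "propensity score matching will be applied to further assess robustness of the primary findings".

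**The concern.** For a patient who already lives in an institution, the destination is largely settled before surgery. Going back there is no change. For a patient who lived at home, discharge to long-term care is a new admission. The planned table puts both in one cell, so a difference in that cell between the cohorts has two possible sources: what happened after surgery, and who was admitted in the first place.

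Allocation is by hospital, three in School A and four in School B. The share of residents in each cohort depends on the catchment areas of a few hospitals, and randomization does not balance it. Any difference in that share would pass into the unadjusted comparison and could be reported as an effect of surgical timing on discharge destination.

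**Working it through.** **The plan's own figure.** The article gives no figure for discharge destination. The group size used below is the one in section 5.7, and it reproduces: (1.645 + 1.282)² × (0.15×0.85 + 0.10×0.90) / (0.05 + 0.05)² = 8.567 × 0.2175 / 0.01 = 186.3, so 187 per group and 374 in total.

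**Inputs from the documents.** Five categories (section 5.5.2), so the chi-square test has 4 degrees of freedom; 187 per group (section 5.7).

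**Assumptions, not in the documents.**
- Two-sided 5% level.
- Timing has no effect.
- Every institutional resident returns to long-term care.
- Other patients have the same destination mix in both cohorts, and a fraction c of them goes to long-term care. I take c = 0%, 5% and 10%.
- Resident shares of q_A and q_B in the two cohorts.

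**Formula.** The expected share in the long-term care cell is L = q + (1 − q)c in each cohort. The other four cells shrink in proportion. With h = half the difference between L_A and L_B, and M = their mean, the noncentrality of the chi-square test is

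λ = 374 × h² × [1/M + 1/(1 − M)].

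The way the remaining patients split over the other four destinations drops out. The rejection probability is the chance that a noncentral chi-square variable with 4 df and noncentrality λ exceeds 9.488.

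**Worked case, 20% v 30% with c = 5%.**
- L_A = 0.20 + 0.80×0.05 = 0.240 and L_B = 0.30 + 0.70×0.05 = 0.335.
- h = 0.0475 and M = 0.2875.
- λ = 374 × 0.002256 × (1/0.2875 + 1/0.7125) = 2.935 + 1.184 = 4.12.
- Rejection probability 33%.

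**Results over the range.**

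| Resident shares | c = 10% | c = 5% | c = 0% |
|---|---|---|---|
| 20% v 20% | 5% | 5% | 5% |
| 20% v 22% | 6% (λ = 0.15) | 6% (λ = 0.18) | 6% (λ = 0.23) |
| 20% v 25% | 10% (λ = 0.90) | 11% (λ = 1.09) | 13% (λ = 1.34) |
| 20% v 30% | 28% (λ = 3.45) | 33% (λ = 4.12) | 40% (λ = 4.99) |

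**Check by simulation** (c = 5%, 4,000 runs each). Equal shares of 20% rejected in 4.75% of runs. At 15% v 25% the formula gives 37% and the simulation 36%. At 15% v 30% the figures are 70% and 72%.

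**Does the test rank the destinations?** No. For an example table of five destinations by two cohorts, the chi-square statistic was 3.418, and it was 3.418 again after the columns were put in another order.

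**The case against.** Several counter-arguments carry weight.

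*The outcome is legitimate as it stands.* Section 5.5.2 announces resource use among the secondary outcomes, and for that purpose the raw destination is a proper measure. This stands, and it is why the raw categories should stay in the report. It does not help with attributing a difference in destination to timing, which is what the objective in section 4.2 asks for.

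*No imbalance is shown.* Section 5.2 argues that patients reach hospitals independently of their characteristics and that the centers are comparable. This stands as far as it goes: the distortion is conditional, and at 20% v 22% it is negligible. But sections 1 and 5.2.1 concede residual confounding, and this potential confounder is measured, so there is no need to rely on the expectation.

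*Every secondary outcome is tested without adjustment.* True, and imbalance would affect the others too. Discharge destination differs in that one recorded baseline variable nearly determines the outcome for a whole subgroup.

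*This is detail for an analysis plan.* Cross-tabulating by a baseline variable often is. Here, however, the article itself fixes the categories and assigns an unadjusted test to outcomes of this kind.

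Three stronger readings are tempting and lack support. A reader might infer that a returning resident is scored as having the worst outcome. No section ranks the destinations, long-term care is merely listed last, and the chi-square test ignores order. A reader might infer that the plan sets out to measure loss of independence and that residents dilute the effect. No objective in section 4.2 names that. A reader might also test long-term care against all other destinations. At 20% v 30%, with that class holding residents only, SE = √(2×0.25×0.75/187) = 0.0448, z = 2.23, and the rejection probability is Φ(2.23 − 1.96) = 61%. The arithmetic is right, but that is not the planned five-category test, for which the figure is 28–40%.

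**Conclusion.** The point holds in a limited form. As specified, the comparison cannot separate a return to an institution from a new admission, and it is open to any difference in prior residence between two non-randomized groups of hospitals. The consequence runs from almost nothing with a 2-point difference in resident share to a rejection rate of 28–40% with a 10-point difference. All of these figures rest on assumed resident shares and on residents always returning to long-term care. The documents neither give a share nor show an imbalance, so they do not support a claim that the result will be biased. Only one secondary outcome is affected. This is a cheap improvement.

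**What to change.** Compare discharge destination stratified by pre-fracture living situation, for example with a Cochran–Mantel–Haenszel general association test, or with a regression that has living situation as a covariate. Show the five destination categories by cohort within each level of prior residence.

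As a supplement, restrict to patients who were not in an institution before the fracture and report the risk difference with a 95% CI for new discharge to a long-term care facility. Show temporary nursing and rehabilitation stays as a separate class, because the plan does not say whether they count as a higher level of care.

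Both variables are already in the planned data set, and inclusion is expected to run until June 2027, so the change can be fixed before analysis. The cost is slightly more analysis work, and residents leave the supplementary comparison.
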